### Assessment Procedures

#### activPAL Procedure

At baseline, the activPAL monitors and required adhesive materials (several Hypafix patches and alcohol swabs) will be provided to participants during a face-to-face assessment session. An in-person demonstration will be given at this session on how to wear the device (ie, on the dominant thigh on the midline, approximately one-third of the way down between the hip and the knee, attached using hypoallergenic adhesive material (Hypafix)). Participants will be asked to wear the monitor for seven consecutive days, 24 hours per day, removing only in circumstances during which the monitor is likely to be lost or damaged, but not for routine showering/bathing or swimming, as monitors will be waterproofed (with latex finger cots and hypoallergenic Opsite). Instructions will also be sent by email. Participants not able to attend the face-to-face baseline assessment session will receive an activPAL from the workplace champion after the session. At follow-up assessments, the activPALs will be distributed to participants by the workplace champion (site A) and either the workplace champion or by project staff to participants at site B. Site A participants will be instructed to return their monitor in sealed packs to the workplace champion, who will post these packs to project staff for download and processing. Site B assessment packs will be collected in person by project staff.

Concurrent diaries, covering waking hours, periods wearing/removing the activPAL, work days and times that are similar to previous paper-based versions [39,58] will be piloted in electronic forms (via LimeService and via a macroenabled excel-based file), with paper versions provided as an alternative option for those experiencing any difficulties with the electronic versions. The diary for Group 2 participants at 3-month follow-up will also cover LUMOback wear/removals, frequency of checking the LUMOback app, usage, and setting type of the vibrations and sitting time alerts, and usage of goal setting over the 7-day assessment period. Participants who do not complete all aspects of their diary will be recontacted to provide further details.

#### activPAL Data Processing

The measures for activity overall and activity during work hours will be extracted from the events-based activPAL data using procedures similar to a previous study [58] via a customized SAS program (version ≥9.3). Activity recorded by the activPAL during relevant periods (eg, working, awake, and wearing the monitor) will be ascertained from a combination of the diary information and the participant’s movement as recorded by the activPAL. When wear/waking hours are not reported, these will be inferred from the movement data. Bouts of activity will be assigned the classification (eg, awake/not, working/not) that applies to most (≥50%) of the bout. Sleeping periods will be adjusted to exclude any short bouts (<20 minutes duration) at the beginning or end of the sleeping period. Studies use a variety of definitions for ‘valid’ days of activPAL data [76]. Days will be considered valid for activity at work if the activPAL was worn for ≥80% of the time at work; entire waking days will be considered valid for activity if the activPAL is worn for ≥80% of waking hours and for ≥10 hours if waking hours are inferred from the activPAL rather than reported by the participant. Time spent in each activity will be calculated for each day then averaged over the valid days. Information about duration of bouts of activity (eg, usual sitting bout duration) will be calculated across all of the relevant time periods on valid days.

Quality control checks will be performed both prior to processing for the diary (missing information, nonconsecutive dates, activities finishing prior to starting, short waking days <10 hours), and postprocessing. The processed data will be checked visually (heatmaps) to verify the activity patterns were consistent with the classifications of the data as included (waking wear on valid days) or excluded (removal, sleep, or invalid days) and data will be reprocessed when errors are identified.

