### Randomization

Following manager consent, and prior to the information session, each team will be numbered randomly, using a random number generator, and then listed in numeric order. Teams will then be randomized to either Group 1 (organizational-level strategies only) or Group 2 (organizational-level strategies plus activity tracker), across location strata (site A and B) and team size strata within site A (small/large) using a randomization website [56]. The randomization schedule will be created by a university staff member not involved in the study. A project staff member will then apply the randomization schedule to the list of teams. Neither project staff nor participants will be blinded to participants’ randomization condition.

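### The visual check and reprocessing of activPAL classifications is not masked to group, leaving a small, avoidable opening for bias, mainly in overall sitting time

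*Protocol article*

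**What the plan says.** Four parts of the Methods bear on this.

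- **Randomization:** "Neither project staff nor participants will be blinded to participants’ randomization condition".
- **activPAL Procedure:** site A monitors go back to the workplace champion, "who will post these packs to project staff for download and processing"; site B packs are collected by project staff. "The diary for Group 2 participants at 3-month follow-up will also cover LUMOback wear/removals", so that diary identifies the group. Participants with incomplete diaries are contacted again.
- **activPAL Data Processing:** a SAS program builds working, waking and wear periods from diary and movement data. Missing waking or wear hours are inferred from movement. Bout assignment, sleep edges and valid days follow numeric rules, for example "Days will be considered valid for activity at work if the activPAL was worn for ≥80% of the time at work". A visual step then follows: "The processed data will be checked visually (heatmaps) to verify the activity patterns were consistent with the classifications of the data". The labels under review decide which time counts: waking wear is kept if the day is valid, while sleep, monitor removals and days that fail the rules are dropped. Where the checker finds a mistake, the file is run again.
- **Activity Outcomes:** the two primary outcomes are sitting at work and sitting across all waking hours, and the activPAL category called sitting also contains lying.

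The article states no masking of group for the visual check.

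**The concern.** An objective monitor does not by itself make the outcome objective. Because lying counts as sitting, an hour relabelled from sleep or removal to waking wear can add up to an hour to that day's overall sitting. Those are the labels that the heatmap check confirms or overturns. The text leaves that judgement to people who may know the group.

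Two estimates are at stake. The primary effectiveness aim is a change from baseline within each group, and Methodological Considerations concedes that there is no untreated control. A consistent lean in the follow-up files only would therefore enter the primary estimate in full. A lean in one group only would enter the secondary between-group comparison. Participants in this trial cannot be blinded, but the person looking at a heatmap can be kept unaware of group.

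**Working it through.** **Where the discretion lies.** The valid-day rules (80% of work time; 80% of waking hours, plus 10 hours if waking time is inferred), the 50% bout rule and the 20-minute sleep-edge rule are fixed and programmed. They act, however, on sleep, wear and work periods built from diary and movement. Judgement enters when a gap in the diary is resolved and when a displayed classification is called an error.

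**Which outcome is exposed.** Overall sitting is exposed through both sleep and removal labels. Work sitting is bounded by work times and depends little on sleep boundaries, so its exposure is smaller.

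**The plan's own figure first.** Inputs from Sample Size and Table 2: 75 per group, 30% attrition, ICC 0.1, 5.83 participants per team, SD 90, pre-post correlation 0.6, minimum difference of interest (MDI) 45 minutes.

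- n per group = 75 × 0.7 = 52.5
- design effect = 1 + 0.1 × 4.83 = 1.483
- effective n = 52.5 / 1.483 = 35.4
- SD of change = 90 × √(2 × (1 − 0.6)) = 80.5
- SE of within-group change = 80.5 / √35.4 = 13.5 minutes
- power for 45 minutes, two-sided 5%: 89.8% by noncentral t (91.4% by normal approximation). Table 2 states 90%, so the figure reproduces.
- SE of the baseline-adjusted group difference = 90 × √(1 − 0.6²) × √(2 / 35.4) = 17.1 minutes

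**Size of a possible lean.** The article gives no edit rate, so these inputs are assumptions: 5% to 20% of person-days altered at one wave, each moving 30 to 60 minutes in the same direction. Shift in the wave mean = fraction altered × minutes moved.

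| Fraction of days | Minutes moved | Shift (min) | Share of 45-min MDI |
|---|---|---|---|
| 0.05 | 30 | 1.5 | 3% |
| 0.10 | 60 | 6 | 13% |
| 0.20 | 60 | 12 | 27% |

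**Effect on the within-group test when there is no true change.** With shift b, the rejection probability is Φ(b/SE − 1.96) + Φ(−b/SE − 1.96).

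- b = 6: b/SE = 6 / 13.53 = 0.443; Φ(−1.517) + Φ(−2.403) = 0.065 + 0.008, about 7%
- b = 12: b/SE = 12 / 13.53 = 0.887; Φ(−1.073) + Φ(−2.847) = 0.142 + 0.002, about 14%

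For larger leans, outside the assumed range, 15 and 20 minutes would give about 20% and 32% within group, and about 14% and 22% between groups.

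**The case against.** The case on the other side is substantial, and much of it stands.

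- **The validity rules are not discretionary.** Correct. A reader might infer that staff choose which days count. The article does not support that: the thresholds are numeric and applied by a program, and the visual step is described as verification.
- **The article does not say who reads the heatmaps.** Correct. The sentence is passive. That unblinded project staff do it is an inference from their receiving the monitors for processing. Nothing assigns it to a masked person either.
- **Masking the wave is not workable.** Correct. Individual feedback follows each assessment, and interviewees at 3 months are sampled partly on change in sitting time. Each wave must therefore be processed as it arrives, with results linked to participants. Hiding wave, or locking all data before wave is attached, would conflict with the plan.
- **The check is not the only subjective step.** Correct. Work, waking and wear times come first from diaries kept by unblinded participants, and masking the checker leaves that untouched.
- **The magnitude is assumed and modest.** Correct. The whole 1.5 to 12 minute range is below one standard error (13.5 minutes), and edits that lean equally at both waves cancel in a pre-post change.
- **A condensed article may leave error criteria and edit logs to another document.** Fair, so their absence is not itself the point. The point is that a visual check with reprocessing is specified in a trial that declares its staff unblinded.

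What survives is narrower: group can be masked at this step at little cost, and the effect of the corrections can be shown even though wave cannot be masked.

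**Conclusion.** The point holds as a cheap improvement to the method, not as an error in the plan. No figure is wrong, and Table 2's power for the primary outcomes reproduces. A reader might infer that the primary results are biased by editing. The article shows only that a lean is possible; it gives no sign that one occurred and no information on its size.

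Under the assumed edit rates, and only if every edit runs in one direction at one wave, the shift is 1.5 to 12 minutes, or 3% to 27% of the MDI. The within-group false-positive rate would be about 7% at 6 minutes and 14% at 12. The low end is negligible; the high end is worth preventing in an uncontrolled pre-post comparison. The exposure is mainly in overall sitting. The conclusion also assumes that the heatmap check falls to project staff or to someone else aware of group.

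**What to change.** In activPAL Data Processing, state that:

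1. heatmap checking and any reprocessing are done on ID-coded files that do not show group, using a diary extract from which the LUMOback fields have been removed;
2. the same error criteria apply at every wave;
3. each edit is logged, and the number of edited person-days is reported by group and wave;
4. the primary pre-post analyses and the between-group analyses are repeated on the SAS output before visual correction, as a sensitivity analysis. This covers the wave-related risk that masking cannot remove.

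Feedback after each assessment, diary recontact and interview sampling can go on as planned. No extra staff, visits or participants are needed. The article reports data collection as finished with results still awaited, and none of this needs new data. The cost is a little data-management and analysis time.

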#### Questionnaire Procedure

At baseline, 3-, and 12-month assessments participants will be emailed a link to a Web-based questionnaire (LimeService) by project staff after they have finished wearing the activPAL. At baseline, questionnaires are to be completed before the intervention begins. At all stages, participants will be provided with the opportunity to opt out of the questionnaire.

#### Qualitative Interview and Focus Group Procedures

Semistructured telephone interviews will be conducted at the 3-month assessment. Attempts will be made to contact all participants in Group 2, with a similar number of participants recruited from Group 1, sampling purposively for diversity, starting with the two most disparate team members per team on age, gender, job category, and sitting time change. All team managers will also be approached for a telephone interview. All interviews will include questions to evaluate the organizational support intervention; Group 2 interviews will also assess the LUMOback. Interviews will be recorded using Audacity (version 2.0.6) and transcribed verbatim with idiosyncratic elements of speech removed. All participants who remain in the study at 12-month follow-up will be invited to take part in focus group interviews, which will be capped at 10 participants each. Participants will be offered a chance to win an activity tracker (single prize; randomized prize draw; value ~AU$500) for participating in the focus groups. Focus group interviews will be audio-recorded and transcribed.

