A LUMOback and a four-page instruction booklet that covers an introduction to the device, set-up instructions, and frequently asked questions will be distributed to Group 2 participants by the workplace champion following baseline assessments. On receipt of the device, participants will be asked to download the free app and sync the LUMOback with their phone. Participants will be asked to use their work email to set up their device as this will later be used to request the data from the company LUMO Bodytech. Participants can wear the device as much or as little as they like and their self-directed usage will be tracked. However, participants will be instructed by project staff to wear their LUMOback during the 3-month assessment period both to gather validity data and to estimate the intervention effectiveness while wearing the LUMOback. Participants will be allowed to keep the LUMOback.

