### Data Collection

Data collection will occur at baseline, 3, and 12 months, and has been approved by the organization to occur during work hours. At each assessment, participants will be asked to wear an activPAL3 activity monitor continuously (24 hours/day) for 7 days, and to complete a concurrent electronic work and sleep diary. They will also be emailed a link to a Web-based questionnaire, using LimeService [63] covering demographic information (baseline assessment only), health- and work-related information (all assessments), and feasibility and acceptability (3- and 12-month assessments). Height and weight will be measured by a trained Lendlease staff member (site A) or project staff member (site B) during a face-to-face baseline assessment session that is expected to take approximately 15 minutes.

Individual qualitative interviews on the feasibility and acceptability of both of the interventions will occur following the 3-month assessment via telephone. Focus groups covering the long-term feasibility and acceptability of the interventions will be conducted as part of the 12-month assessment. Project staff will request LUMOback usage data from Lumo Bodytech every 2 weeks during the initial 3-month intervention period and then periodically throughout the rest of the study.

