#### Acceptability

Participants will be asked via questionnaire to rate how useful the emails and tips were, their satisfaction with the emails and information, and if they had experienced any discomfort or injury as a result of their study participation. Participants who indicate they have used a LUMOback device will also be asked to rate their comfort, ease of use, and perceived usefulness of the LUMOback (see Multimedia Appendix 1 for full list of questionnaire items). Participants who indicate they were given a LUMOback (whether they wore it or not) will also be asked would they recommend the LUMOback to a friend, how likely they were to use the LUMOback in the next 6 months, did they have any adverse experiences from using the LUMOback, and if they had any comments about the LUMOback or app. A shorter questionnaire at 12-month follow-up (to reduce participant burden and maintain compliance) will collect information relating to long-term LUMOback usage, adverse experiences, and comments. Telephone interviews and focus groups will also assess the acceptability of both interventions over the short and long-term (see Multimedia Appendices 2 and for questions).

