##### Work Outcomes

Work-related outcomes will be measured via questionnaire at all assessments. These are work performance [69] and two measures from the Health and Work Questionnaire [68]: work satisfaction (four items, with α for internal consistency=0.84), and job control (one item).

**Table 1 table1:** Overview of study outcomes.

Measurement tools	Outcomes
Feasibility
Organizational support questionnaire items	Number of emails received
	What participants did with email (eg, read then delete)
	Perceived level of support to ‘Stand Up, Sit Less and Move More’ from (1) organization, (2) main manager, and (3) colleagues
LUMOback questionnaire items	Ever used (eg, yes, given but never used, no)
	Date of first use
	Setting of use (eg, workplace)
	Frequency of recalibration, app checking, goal checking, vibration and sitting alerts
LUMOback data	Days of usage
	Hours of usage/day
	Peak levels of usage
	Ease of data download
	Amount of missing data
Telephone interviews	Strategies implemented by manager and organization, organizational culture change, key elements of intervention, barriers of wearing the LUMOback at work and at home
Focus groups	Long term sustainability of changes, barriers and facilitators, key themes
Acceptability
Organizational support questionnaire items	Usefulness of emails and tips
	Satisfaction with emails and information received
	Adverse experiences from program in general
LUMOback questionnaire items	Comfort of LUMOback
	Ease of set up of LUMOback and app, navigating app, calibrating LUMOback
	Usefulness of LUMOback and app
	Likelihood of using LUMOback in next 6 months, adverse experiences from LUMOback, comments about the LUMOback
Telephone interviews	Acceptability of program, acceptability of the LUMOback
Focus groups	Acceptability of program, acceptability of long-term LUMOback wear
Effectiveness
Activity
activPAL	Stand up: standing time at work and overall
	Sit less: sitting time at work and overall (primary effectiveness outcomes); prolonged (>=30 mins) sitting time at work and overall
	Move more: stepping time at work and overall
Health
SF-12 v1	Physical and Mental health-related quality of life	
Health and Work Questionnaire	Overall stress
Work
Work performance rating scale	Work performance
Health and Work Questionnaire	Work satisfaction, job control

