## Discussion

This paper describes the background, design, and methods of a pilot, cluster-randomized trial that will compare two interventions, one that targets organizational-level strategies and another that targets organizational-level strategies plus the use of a wearable activity tracker, the LUMOback, in office workers. The study will determine if either intervention can produce changes in sitting (during all waking hours and work hours), as well as prolonged sitting, standing, and stepping in the short (3 month) and long-term (12 month), as well as the feasibility and acceptability of each intervention. The impact of each intervention on health- and work-related outcomes, and the predictors of sitting and activity change will also be examined. In addition, the study will provide preliminary evidence regarding the additional impact of the LUMOback on sitting and activity compared with organizational-level strategies alone.

The interventions in this study are designed to be easily disseminated on a large scale. Specifically, the intervention elements will come from the Head of Workplace Wellbeing, making the implementation of the intervention similar to that which may realistically occur in office workplaces. The intervention messages are delivered via a low cost, feasible mechanism (emails), with the LUMOback device also being relatively low cost, and comparable in price with other popular fitness trackers on the market (~US$150). Another strength of the intervention is that support and participation will come from multiple levels of the organization (ie, general staff, managers, senior global executives). In addition, sitting, standing and stepping will be measured at and away from the workplace, with a validated and objective measure. Many workplace studies have only measured workplace activity, and have often not used objective, posture-based measures.

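### The prize draw for attending the 12-month focus groups is for an activity tracker, the class of product whose long-term acceptability they help to judge, so attendance may depend on attitude to trackers

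*Protocol article*

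**What the plan says.** Under Qualitative Interview and Focus Group Procedures, the incentive reads: "Participants will be offered a chance to win an activity tracker (single prize; randomized prize draw; value ~AU$500) for participating in the focus groups". The invitation is open: "All participants who remain in the study at 12-month follow-up will be invited to take part in focus group interviews". Each group is capped at 10 people. Neither selection for diversity nor balance by trial arm is mentioned.

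The purpose appears under Data Collection: "Focus groups covering the long-term feasibility and acceptability of the interventions will be conducted as part of the 12-month assessment". The acceptability block of Table 1 lists for the focus groups: "Acceptability of program, acceptability of long-term LUMOback wear".

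Two other 12-month sources bear on the same question. The Acceptability section describes a shortened questionnaire that "will collect information relating to long-term LUMOback usage, adverse experiences, and comments". Data Collection has LUMOback usage data requested "every 2 weeks during the initial 3-month intervention period and then periodically throughout the rest of the study".

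On the devices, Group 2 members own theirs ("Participants will be allowed to keep the LUMOback"), and the Discussion describes the LUMOback as "comparable in price with other popular fitness trackers on the market (~US$150").

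**The concern.** An incentive should be unrelated to the opinion being collected. Here it is a product of the same class as the one under judgement, so it plausibly appeals more to people who like trackers than to people who gave up on one. If so, the chance of attending depends on the attitude that the groups are meant to reveal.

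The 12-month groups have little stated protection against this. For the 3-month telephone interviews, the plan tries to reach everyone in Group 2 and picks Group 1 members to be varied. Nothing comparable is stated for the focus groups, and the people invited have already passed a separate reconsent step for the 12-month assessment.

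At stake is the balance of themes on long-term acceptability. The 3-month questionnaire asks Group 2 users how comfortable, easy and useful the device was. The shortened 12-month version is not described as repeating those ratings, so the focus groups carry much of the 12-month acceptability evidence, though not all of it. Methodological Considerations covers the missing control group, contamination and selection of teams, but not selection through the prize.

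**Working it through.** The plan gives no figure for focus-group attendance or opinion, so there is none to reproduce. Two short calculations show the scale.

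**1. How strong is the incentive?** Inputs: one prize of about AU$500 (Qualitative Interview and Focus Group Procedures); 150 participants and 30% attrition (Sample Size). The attrition figure belongs to the 3-month calculation. Retention at 12 months is not stated, so 150 × (1 − 0.30) = 105 serves only as a nominal upper end. With k attendees, the chance of winning is 1/k and the average value of an entry is AU$500/k.

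| Attendees k (assumed) | Chance of winning | Average value |
|---|---|---|
| 10 | 10% | AU$50 |
| 20 | 5% | AU$25 |
| 40 | 2.5% | AU$12.50 |
| 105 | 0.95% | AU$4.76 |

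**2. How far could attendance shift the mix?** Let p be the share of invitees favourable to trackers, and R the attendance rate of favourable people divided by that of the rest. The favourable share among attendees is pR / (pR + 1 − p). The documents give neither p nor R; all values below are assumptions.

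- p = 0.5, R = 1: 0.50/1.00 = 50% (no shift)
- p = 0.5, R = 1.1: 0.55/1.05 = 52%
- p = 0.5, R = 1.25: 0.625/1.125 = 56%
- p = 0.5, R = 1.5: 0.75/1.25 = 60%
- p = 0.5, R = 2: 1.00/1.50 = 67%
- p = 0.3, R from 1.1 to 2: 0.33/1.03 = 32% to 0.60/1.30 = 46%
- p = 0.7, R from 1.1 to 2: 0.77/1.07 = 72% to 1.40/1.70 = 82%

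If the prize drew people who disliked the LUMOback, R would be below 1 and the shift would reverse: p = 0.5 and R = 0.8 gives 0.40/0.90 = 44%.

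These figures show the mechanism only. Feasibility and Acceptability, under Statistical Analyses, plans a thematic analysis of the focus groups, so no favourable share is estimated. The practical effect would be on which themes surface and how prominent they are.

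**The case against.** The strongest reply is that the documents show no bias, only an incentive that might cause one. Most of this stands.

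- A reader might infer that everyone who attends receives a tracker. The text offers one entry in a single-prize draw, and entry depends on attending, not on the views expressed.
- A reader might infer that the prize is worth nothing to someone who disliked tracking. It could be sold or given away. It also appears to be a different, dearer device: AU$500 and US$150 would be the same price only at 500/150 = AU$3.33 to the US dollar (the documents give no exchange rate). Someone who disliked a posture belt might still want it.
- A reader might infer that the pull differs by arm in a way that favours the LUMOback. The direction is unclear. Group 1 was issued no LUMOback, so drawing in more of Group 1 adds few people who can judge wearing one. Group 2 already owns a tracker, so the pull may be weakest where opinion matters most.
- The focus groups are not the only 12-month source. Neither the questionnaire nor the device data depend on attending.
- Voluntary focus groups are self-selected under any incentive.

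What remains is narrower. Self-selection in general is unavoidable, but an incentive of the same class as the product under evaluation is an added and avoidable link. The other 12-month sources measure mainly usage and harms and do not replace the discussion of acceptability. Transcripts cannot recover the views of people who stayed away, although data already collected can show whether those people differed at 3 months.

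**Conclusion.** The point holds as a minor design weakness. The prize creates a possible selection effect on one qualitative source for a secondary aim. The likelier direction is towards acceptance, on the assumption that interest in winning a tracker goes with a favourable view of trackers; the documents neither confirm nor exclude that. The size cannot be derived.

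A reader might conclude that long-term acceptability is overstated. The documents do not support this: they report no attendance or opinions, the draw is a weak incentive, and the reverse direction is possible. Nor does the point reach the primary outcomes, which are activPAL sitting times and unconnected with the prize.

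**What to change.** **In the plan, or in any successor trial:** replace the prize under Qualitative Interview and Focus Group Procedures with one of the same value unrelated to activity tracking, such as a general gift card. The value and the draw stay as they are, so the cost is essentially nil.

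**In this trial:** the Results section says data collection has finished, so if the draw has taken place the prize cannot be changed. Three reporting steps remain:

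1. Give the numbers invited to and attending the focus groups, by group.
2. For Group 2, compare attendees with non-attendees on the 3-month LUMOback ratings and on logged usage. Show people who did not reconsent for 12 months separately from those invited who did not attend. Keep this descriptive, as numbers will be small.
3. Name the prize under Methodological Considerations as a possible source of selection.

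The cost is one small table from data already held, provided that attendance was recorded, and a sentence or two of text. Similar groups in step 2 would ease the concern without excluding selection on attitudes formed after 3 months.
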